## Abstract

**Background:**

In 2020, the German Federal Constitutional Court declared the criminal prohibition of assisted suicide as unconstitutional, thereby abolishing previous restrictions. Since then, requests and cases have increased steadily. To ensure transparency and traceability of national assisted suicide practices, systematic and reliable data are required. However, no comprehensive registry currently exists to document and analyze assisted suicide cases in Germany, resulting in a significant data gap for epidemiology, health reporting, and healthcare development. The development, implementation, and evaluation of such a registry is essential to better understand current practices, identify challenges, and improve prevention and support strategies.

**Methods:**

Iterative, mixed-methods, design-based implementation study with five work packages: 1. conceptual, ethical, and legal development of registry content through a scoping review and a group Delphi process; 2. establishment of the legal, ethical, and technical framework of the registry using an iterative, design-based approach; 3. evaluating and refining the registry through a formative mixed-methods design combining quantitative user surveys and web analytics with qualitative think-aloud and retrospective interviews; 4. exploring barriers to the adoption, continuation, and use of the registry through quantitative surveys and in-depth qualitative interviews with potential users; 5. strategic development, dissemination, and integration of the registry within existing healthcare and suicide prevention structures. The study involves expert consultations and stakeholder engagement and is conducted by a multidisciplinary consortium of palliative care and suicide prevention experts in Germany.

**Discussion:**

The establishment of a permanent registry for assisted suicide could substantially improve transparency and empirical knowledge in a highly sensitive and ethically complex field. Systematic documentation may help identify needs, vulnerabilities, and structural challenges faced by individuals considering assisted suicide. In the long term, the findings derived from the registry are expected to contribute to the development of targeted support services in Germany. The study results may also provide valuable insights for other countries facing comparable ethical, legal, and regulatory challenges.

**Trial registration:**

Registered on 25 October 2025 in the BQS (Institute for Quality and Patient Safety) registry, No. 2020467 and on 29 April 2026 in the German Clinical Trials Register (DRKS), No. DRKS00040174.

**Supplementary Information:**

The online version contains supplementary material available at https://doi.org/10.1186/s12910-026-01591-4.

## Background

In 2020, the German Federal Constitutional Court declared Sect. 217 of the Criminal Code, which had prohibited commercial assisted suicide, to be unconstitutional [1, 2]. The Court emphasized that the right to a self-determined death includes the freedom to seek and accept assistance from third parties, regardless of a person’s life situation and not only to people with life-limiting illness [1]. Since then, a steady increase in assisted suicide cases has been reported in Germany [3, 4].

Overall, suicide rates in Germany have declined markedly since the 1980 s but have risen again since 2019, reaching 10,304 deaths in 2023 and increasing further to 10,372 in 2024 [5]. However, official mortality statistics do not distinguish between assisted and non-assisted suicides, limiting reliable monitoring. Available data from individual sources point to a dynamic development: the largest organization in Germany providing assisted suicide reported 898 assisted deaths in 2025 compared to 623 in 2024, with a continuous rise since 2021 [4]. A study on population-based data from the German federal state of Bavaria also indicate a substantial increase in cases since 2020 [3]. Reported data also highlight significant limitations of the current national data infrastructure, as assisted suicide is neither systematically recorded nor separately coded.

In this context, registries on assisted dying are increasingly recognized as important instruments for transparency, accountability, and ethical oversight, as well as for epidemiological research, health reporting, and healthcare system development [6–8]. In countries where assisted dying is legal, structured reporting systems with mandatory notification and independent review enable systematic monitoring of practice. Comparable approaches exist in other jurisdictions, including Austria (www.ascirs.at) and parts of the United States [9–11], where reporting systems provide detailed insights into the circumstances and developments of assisted suicide. In Germany, however, no dedicated registry currently exists, and comprehensive data on affected individuals and the relevant contextual factors are entirely lacking. Given the substantial clinical, ethical, and health care implications of the Federal Constitutional Court’s ruling on assisted suicide, this absence of systematic evidence is striking.

Existing evidence further suggests that assisted suicide differs from conventional suicide regarding sociodemographic and clinical characteristics. For example, the study from Bavaria suggests that individuals who died by assisted suicide were more likely to be older, female, highly educated, socioeconomically advantaged, and to have psychiatric and neurological disorders, particularly depression, neurodegenerative diseases and dementia [12]. Gender differences are well documented in suicide research, with higher non-assisted suicide rates among men and higher rates of suicide attempts among women [13, 14]. In contrast, available data from countries with assisted suicide suggests a more balanced gender distribution [11, 15]. For conventional suicide, a range of additional risk factors has been identified, including gender identity and sexual orientation, with elevated risks among LGBTQI + populations. However, comparable evidence for assisted suicide is largely lacking, highlighting an important gap in knowledge and the need to identify relevant risk groups [16]. Overall, no reliable national data on assisted suicide cases is currently available. Nevertheless, some right-to-die organizations provide descriptive case statistics that, although not independently verifiable, may offer preliminary insights into the motives and circumstances associated with assisted suicide [4].

Against this background, the present study aims to develop, implement, and evaluate a permanent registry for assisted suicide in Germany. Such a registry may enable systematic data collection, improve the empirical basis for ethical and policy debates, and support the development of targeted services and support strategies by identifying relevant risk groups, needs, and patterns over time.

## Methods/design

This study is designed as a 30-month iterative, mixed-methods, design-based implementation project integrating 1. conceptual development, 2. the establishment of an ethical, legal, and technical framework, 3. formative evaluation, 4. exploration of barriers to registry adoption as well as 5. strategic dissemination and integration activities to support the sustainable development and implementation of a national registry for assisted suicide in Germany (see Fig. 1).

**Fig. 1 Fig1:**
[figure not shown]
Overview of the study work packages

### Objectives

The primary objective of this study is to develop, implement, and evaluate a national registry for assisted suicide in Germany.

Secondary objectives are:to establish a consensus-based dataset for the systematic documentation of assisted suicide;to develop a GDPR-compliant ethical, legal, and technical registry infrastructure;to evaluate usability, feasibility, and acceptability of the registry;to identify barriers to registry adoption and sustained use;to support long-term implementation and integration into national suicide prevention and health monitoring structures.

### Outcomes

The primary outcomes of the study are:successful development and implementation of a functional registry platform;usability and feasibility of registry use.

Secondary outcomes include:stakeholder acceptance,completeness and quality of collected data,barriers to registry adoption,usage patterns,and sustainability indicators for long-term implementation.

The study is conducted in cooperation with leading institutions in palliative care (e.g. the German Association for Palliative Medicine, a scientific, multi-professional association with over 6,800 members) and in suicide prevention (e.g. the National Suicide Prevention Programme (NaSPro), a nationwide expert network dedicated to suicide, suicidality, and suicide prevention; and the German Society for Suicide Prevention (DGS), the national professional society for suicidology and suicide prevention in Germany, representing and connecting individuals and institutions active in research, teaching, and practice). Other collaborators include the Austrian Palliative Society (OPG; sponsor of the ASCIRS database), and the German Society for Humane Dying (DGHS) as representative of German euthanasia organizations.

The project team brings together interdisciplinary expertise in palliative care and suicidology. It includes leading experts with extensive research experience, as well as a strong track record in developing and maintaining suicide-related registries. Members of the project team have contributed to national clinical guidelines on end-of-life care [17] and dealing with desire to die [18], and have conducted research on assisted suicide requests and related attitudes among healthcare professionals [19–23]. In addition, the team has experience in the development and evaluation of digital platforms [24] and in methodological aspects of registry research [25], including the assessment of data completeness.

Building on this interdisciplinary expertise, the study is structured into five work packages that guide the development, implementation, and evaluation of the registry.

Figure 1 illustrates the overall structure of the project and its interconnected work packages. Table 1 provides an overview of the main project phases and activities across the 30-month study period.

**Table 1 Tab1:** Overview of project phases and main activities

**Project phase**	**Main activities**
Conceptual development and consensus process (Q1–Q3)	Scoping review and Delphi process for registry development
Technical development and formative evaluation (Q2–Q7)	Development, pilot testing, usability evaluation, and optimization of the registry
Implementation, dissemination, and sustainability (Q6–Q10)	Exploration of barriers to registry use, dissemination activities, and sustainability planning

### Conceptual development of registry content

To establish the basis for the content design of the assisted suicide registry, a scoping review will be conducted to identify, evaluate, and define potential categories and variables. These will then be consented and finalized in a group Delphi process.

#### Scoping review

International databases (MEDLINE, Embase, PsycInfo) will be searched using a predefined strategy combining terms such as assisted suicide, assisted dying, medical aid in dying, registry, database, report, and documentation. The search will be limited to publications from the last ten years (2015–2025) to capture current documentation practices, registries, and databases. In addition, country-specific websites and reports on assisted suicide documentation will be reviewed, including sources from Germany, Austria [26], Switzerland [27], Belgium [28], the Netherlands [29], Spain [30], Canada [31], Oregon (USA) [11], Columbia [32], Australia [33, 34], and New Zealand [35].

From eligible publications and reports, data will be extracted on (1) characteristics of persons who made use of assisted suicide (e.g. age, gender, underlying conditions, reasons for unbearable suffering such as uncontrolled pain, loss of autonomy, functional decline, psychological distress, or loss of dignity), (2) circumstances of assisted suicide (e.g. location, substances used, mode of administration, measures to ensure fulfillment of legal regulations), and (3) characteristics of those providing assistance (e.g. professional background and qualifications). Extracted variables will be organized in a structured matrix. The scoping review will be conducted in accordance with the PRISMA Extension for Scoping Reviews (PRISMA-ScR) [36]. Based on the findings, a preliminary set of candidate variables for inclusion in the national assisted suicide registry will be developed, covering relevant sociodemographic and contextual factors, including gender identity beyond binary categories. This set will be then refined through the subsequent Delphi process.

#### Consensus process using the group Delphi method

Consensus on registry variables will be established using a modified Delphi approach comprising an initial online survey and a subsequent two-day in-person Delphi workshop. The online survey will assess agreement on the proposed variables in a broader panel of experts and identify those items for which consensus has already been achieved. Variables meeting the predefined consensus criteria will be excluded from workshop discussion, enabling a more focused and efficient deliberation of unresolved items while preserving broad expert input.

The group Delphi workshop will involve three to four groups of four to five participants each (*n* = 16–20) [37]. Participants will be purposively selected according to predefined criteria, including professional background, affiliation with relevant organizations, experience with assisted suicide, and involvement as affected relatives, to ensure relevance and applicability. The workshop will be moderated by an independent professional facilitator. Through structured group discussion and voting, individual contributions will be systematically documented, transparently synthesized, and integrated into a final consensus-based variable set for the registry. This approach addresses a known limitation of the traditional Delphi method, in which experts may be reluctant to revise their views based solely on aggregated feedback. The Delphi process will follow the Conducting and Reporting of Delphi Studies (CREDES) recommendations [38].

#### Design and establishment of the registry’s legal, ethical, and technical framework

The registry’s legal, ethical, and technical framework defines the procedures for data collection, processing, and analysis, ensuring data quality, privacy protection, and compliance with regulatory requirements. Therefore, a comprehensive data protection and processing framework will be developed in accordance with the General Data Protection Regulation (GDPR), which constitutes the primary legal basis for this project. This framework defines the required data elements, data minimization strategies, governance structures, cooperation agreements, risk assessments, and organizational and administrative responsibilities. It will also specify the technical infrastructure and procedures for secure data handling and quality assurance.

#### Data collection and technical infrastructure

Data collection is conducted through a secure, web-based questionnaire. Data may be entered into the registry by individuals who have directly participated in or witnessed an assisted suicide (e.g., physicians, family members, representatives of assisted dying organizations), as well as by individuals who considered assisted suicide but discontinued the process. All data is fully anonymized upon entry, ensuring that no individual can be re-identified. Thus, no IP addresses are stored or recorded as direct identifiers of the persons entering the data. Participants are not required to provide personal information. Data are stored on encrypted servers in Germany, with access restricted to authorized project team members. Data is processed exclusively for research purposes. Anonymized data may only be shared with third parties for scientific research, and only after formal review and approval by the project’s steering committee. Such sharing is limited to qualified research institutions and individual researchers and is subject to strict data use agreements.

The content of the registry developed in the first work package captures key information on demographics, motivations, procedural aspects and contextual factors. Once collected, data undergoes a structured processing pipeline. First, data cleaning is performed to identify and resolve inconsistencies, missing values and outliers. This includes automated checks for logical coherence (e.g. age vs. age-related disease) and manual review (e.g. to delete personal information given in a text field).

#### Pilot testing, validation and iterative refinement

Following the development of the technical infrastructure, the registry will be piloted with a group of potential users (e.g. physicians and representatives of assisted dying organizations). During this phase, real cases (where ethically permissible) and theoretical case vignettes will be documented to assess feasibility, usability, and data quality. This approach allows early identification of technical and procedural challenges and supports optimization prior to full implementation.

Based on the findings from the pilot phase and validation procedures, iterative technical and content-related refinements of the registry will be implemented. This includes adjustments to the questionnaire design, data entry interface, and underlying data processing framework to improve usability, data quality, and completeness.

#### Data processing

The cleaned and validated dataset is then used for statistical analysis. Descriptive statistics, trend analyses and subgroup comparisons are conducted to explore patterns in motivations, demographics and procedural aspects. Multivariate models are applied to identify associations between variables with the overarching aim of identifying trends, regional differences and risk profiles among individuals considering or undergoing assisted suicide, ultimately contributing to the development of a comprehensive national registry on assisted suicides and evidence-based support strategies for vulnerable groups.

Data validity and completeness will be assessed through comparison with external data sources, such as death certificates, and by applying capture–recapture methods to estimate potential underreporting.

### Formative mixed-methods evaluation of the registry

To assess usability, acceptability, and feasibility, a formative mixed-methods evaluation will be conducted. Combining quantitative and qualitative approaches enables the capture of both user satisfaction and in-depth user experiences and is well established in the evaluation of digital health platforms [39].

#### Quantitative component of the evaluation

An online survey will be integrated into the registry platform. After completing registration, users will be invited via a pop-up window to participate in a short online survey in which they can voluntarily and anonymously evaluate their satisfaction with, and perceptions of the user-friendliness, the perceived clarity, and efficiency of data entry. Data security and sustainability aspects are considered just as much as the actual motivation for using the register. The target sample size is approximately 50 to 100 respondents. In addition, an integrated analysis tool will be used to collect aggregated web statistics (e.g. time required) to evaluate effectiveness and usage patterns.

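### On the likelier reading, the usability survey behind a primary outcome reaches only users who finish an entry, so its ratings probably overstate usability among all who start

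*Protocol article*

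**What the plan says.** The Outcomes section lists "usability and feasibility of registry use" among the primary outcomes. The section on the quantitative component of the evaluation describes the survey that rates it: "After completing registration, users will be invited via a pop-up window to participate in a short online survey". Participation is voluntary and anonymous ("they can voluntarily and anonymously evaluate their satisfaction with" the registry), and the items cover user-friendliness, clarity and efficiency of data entry. No other access route to this survey is described. Its size is set as follows: "The target sample size is approximately 50 to 100 respondents". The same section adds an analytics tool to "collect aggregated web statistics (e.g. time required) to evaluate effectiveness and usage patterns".

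Other components sit around this survey:

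- **Pilot testing:** potential users try the registry before full implementation.
- **Think-aloud sessions:** five to ten users are observed while using the platform.
- **Barriers survey:** five closed and two open questions on why people stop or avoid using the register. About 20–30 surveys are expected, reachable by a pop-up link and permanently on the website.
- **Interviews:** 10–20 are planned, and they include people who broke off an entry.
- **Triangulation:** the survey and interview findings on barriers are to be integrated.

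**The concern.** An invitation that appears only after success samples on the outcome it is meant to measure. A user defeated by the form does not rate its clarity or efficiency, and a user who found it easy may. If abandoners would have rated the registry lower, the survey result is too favourable. A larger sample does not help, because the missing group stays missing. The plan itself expects abandonment, since it recruits people who broke off an entry for interview.

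At stake is the description of a primary outcome. The registry could report high satisfaction among finishers while the experience of those who dropped out is known only through reasons and narratives, on different questions. Lay users such as relatives may be affected more than professionals who report often, although the documents give no data on this.

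**Working it through.** **Step 1: what does *completing registration* mean?**

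- *Finishing a case entry.* The survey asks about efficiency of data entry, which a user can judge only after entering data. The section on data collection and technical infrastructure describes no user account and asks for no personal details from those who enter data.
- *Signing up as a user.* People who later abandon an entry would then not be excluded, but the pop-up would come before the activity it asks about.

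The first reading fits the text better, and the rest of the check uses it. Under the second, the sentence would still need correcting, for a different reason.

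**Step 2: do other components supply the missing ratings?**

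| Component | Reaches people who struggle or give up? | Described as collecting the same ratings? |
|---|---|---|
| Barriers survey, about 20–30 | Yes; no finished entry needed | No; items on barriers |
| Interviews, 10–20 | Yes | No; qualitative |
| Think-aloud sessions, 5–10 | Observes difficulties directly | No; qualitative |
| Web statistics | Could count unfinished entries | No; usage data, not ratings |

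They can show why people stop. They do not turn a rating among completers into a rating among starters.

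**Step 3: how large could the difference be?** The article gives no derivation for 50 to 100 respondents and no satisfaction or abandonment rates, so there is no figure of its own to reproduce. The inputs below are assumptions: satisfied among completers, *c* = 0.80; share of starters who abandon, *a* = 0.10 to 0.40; satisfied among abandoners, *s* = 0.20 to 0.50.

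All starters: (1 − *a*)*c* + *a s*. Overstatement: *c* − [(1 − *a*)*c* + *a s*] = *a*(*c* − *s*).

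| *a* | *s* | All starters | Overstatement |
|---|---|---|---|
| 0.10 | 0.50 | 0.77 | 0.10 × 0.30 = 0.03 |
| 0.10 | 0.20 | 0.74 | 0.10 × 0.60 = 0.06 |
| 0.20 | 0.50 | 0.74 | 0.20 × 0.30 = 0.06 |
| 0.20 | 0.20 | 0.68 | 0.20 × 0.60 = 0.12 |
| 0.40 | 0.50 | 0.68 | 0.40 × 0.30 = 0.12 |
| 0.40 | 0.20 | 0.56 | 0.40 × 0.60 = 0.24 |

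As a yardstick only, the 95% half-width at 80% is 1.96 × √(0.16/50) = 0.111 for 50 independent respondents and 1.96 × √(0.16/100) = 0.078 for 100. The selection effect can therefore be smaller or larger than sampling error. If abandoners would rate the registry as completers do (*s* = *c*), it is zero.

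**Step 4: person or entry?** The survey is anonymous, and "no IP addresses are stored or recorded as direct identifiers of the persons entering the data". Those who may enter cases include "physicians, family members, representatives of assisted dying organizations", and "the largest organization in Germany providing assisted suicide reported 898 assisted deaths in 2025". So one person could enter several cases, and nothing described would link that person's answers. The article does not say whether the invitation appears once per user or at each entry.

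**The case against.** The strongest reply is that people who give up have not been forgotten. A whole work package is devoted to discontinuation and non-use, with its own survey, interviews and triangulation, and piloting and think-aloud sessions observe difficulties directly. The evaluation is formative, meant to guide refinement, and it states no test, threshold or precision target. That stands. It rules out any claim that the study ignores abandoners or that usability rests on this one survey. It does not make the completer ratings apply to all starters.

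Three stronger readings are tempting and are not supported:

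- *That the survey is answered at every entry and frequent reporters are counted repeatedly.* The text is silent on this, its target is in respondents, and a one-answer rule may sit in the full protocol. Repeat answers are possible, not stated. A design effect would need answers per person and a within-person correlation, and neither is given.
- *That the analytics will record only time.* Time is given as an example, and counts of started and submitted entries fit naturally under usage patterns.
- *That the plan overstates its precision.* It claims none.

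The ambiguity of *registration* also stands, and it limits confidence.

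**Conclusion.** The point holds in a limited form. If the invitation follows a finished case entry, the quantitative ratings behind a primary outcome come only from completers and probably overstate usability among all who start. The other components cover discontinuation but are not described as supplying comparable ratings.

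The illustrated range of about 3 to 24 points rests wholly on assumed rates and on abandoners being less satisfied than completers. It would shrink if people mostly stop for reasons unrelated to usability, such as legal worry or interruption. Repeat answering is a secondary matter to clarify, not an established defect. This is a cheap improvement rather than a fault that undermines the study; confidence is moderate.

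**What to change.** 1. State what *completing registration* means and whether the invitation appears once per user or once per entry.
2. Offer the same short usability items when an unfinished entry is left or times out, or add them to the barriers pop-up already planned. Report the ratings separately for finished and unfinished entries.
3. From the planned analytics tool, report started, submitted and abandoned entries, with the completion proportion and its 95% CI, as a feasibility measure. This needs no answer from those who left. The unit is the entry: a user who breaks off and later restarts counts twice, so the interval is approximate.
4. Add one item asking whether the person has answered this survey before, so that the 50 to 100 target can be counted in persons without weakening anonymity.

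**Cost:** a second trigger or a few items on an existing pop-up, one further question, and counts that the analytics tool would need to be set up to report. The survey becomes slightly longer. Response among abandoners will be low, so their ratings will be imprecise and themselves selective. The completion proportion should therefore be read alongside them.
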